### Recruitment

Recruitment procedures for the Web-based peer support program feasibility RCT are the same as those for the peer mentor training. We will aim to recruit 30 participants. We will recruit caregivers until we achieve the following minimum numbers: (1) ventilator subgroup (invasive: n=2; noninvasive: n=8); (2) diagnostic category (rapidly progressing disease: n=3; nonrapidly progressing disease: n=3; restrictive thoracic cage disorders: n=3); (3) relationship to care-recipient (spouse: n=4; child: n=4; parent: n=4); and (4) gender (male: n=5; female: n=7).

### Allocation

We will randomize consenting participants to the peer support intervention or waitlist control using a 1:1 ratio using Randomize.net. No stratification will be applied, and allocation will be concealed using opaque sealed envelopes. Those randomized to the waitlist control will be given access to the peer support program following the 12-week intervention phase. A waitlist control group was chosen as it is believed to be a cost-effective and ethical alternative to no-treatment control groups when primarily studying psychological and behavioral interventions such as the one in this study [31]. Those randomized to the intervention group will receive information through email about the website features (eg, forum, chat) and instructions in their use, log-in and profile instructions, and the weekly chat schedule. We will send weekly email reminders to encourage participants to access website resources, participate in the weekly chat, and draw their attention to active discussion forum threads.

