### Study Stage 2: Web-based Peer Support Program

#### Objectives

##### Primary Objective

The primary objective is to evaluate the feasibility of trial recruitment and program delivery according to *a-priori* definitions described below and including user ratings of acceptability, usability, and satisfaction.

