### The Web-based Peer Support Program (Intervention)

#### Technical Development

The end goal for this development project was to create a “social-network” style website (akin to Facebook). This website would also need to digitally capture and record all interactions between participants. To provide all the functionality needed for this study (including interaction data capture), we found that nonproprietary “off-the-shelf” software programs or templates were insufficient. Therefore, we used a hybrid of “existing-base-software” coupled with code or programming designed and integrated into this base software, making the functionality of this website unique.

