### Sample Size

There has been no prior assessment of a peer support intervention for VAI caregivers on which to base our sample size calculations. Using feasibility criteria of 15% dropout and 70% participation in weekly chats, a sample size of 30 would allow us to be 90% confident that estimates are accurate within 22% and 28% percentage points, respectively [30].

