#### Upon Program Completion

We will ask participants (intervention arm only) to complete a program evaluation (through telephone or email, depending on preference). The program evaluation will assess the acceptability through a series of questions (eg, about the helpfulness of the program, how likable program was; 5-point Likert scale; generally, 1=very unacceptable; 5=very acceptable). The evaluation will assess satisfaction by asking participants the extent to which they agree with a series of questions about the program content, delivery, and outcomes (5-point Likert scale; 1=disagree; 5=agree) [45]. Finally, the evaluation will assess the usability by asking participants the extent to which they agree with a series of questions about the usability of various program features (5-point Likert scale; 1=strongly disagree; 5=strongly agree) [46]. We will invite participants to complete a semistructured qualitative interview to further explore their experience with the peer support program (eg, which features were most beneficial, what aspects were most challenging, what can be improved, what should be kept the same) and their perspectives on the support received from peers (eg, quality of support, influence on their caregiving experience). We will host 1-2 focus groups with the peer mentors using GoToMeeting. Using a semistructured interview guide, we will explore their experiences and perspectives of the Web-based program as trained peer mentors. Furthermore, we will audiorecord interviews and focus groups and transcribe verbatim.

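### User ratings in the primary objective come from only about half of the caregivers who get the program, and the chat precision stated for n=30 is not reached in the randomized phase

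*Protocol article*

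**What the plan says.** All references are to the protocol article.

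- **Primary Objective (Stage 2):** feasibility of recruitment and program delivery, "including user ratings of acceptability, usability, and satisfaction".
- **Upon Program Completion:** "We will ask participants (intervention arm only) to complete a program evaluation". This evaluation is the instrument for those three ratings. The abstract's Methods carry the same restriction.
- **Recruitment and Allocation:** "We will aim to recruit 30 participants"; "We will randomize consenting participants to the peer support intervention or waitlist control using a 1:1 ratio using Randomize.net". This means about 15 caregivers per arm.
- **Allocation:** the waitlist caregivers "will be given access to the peer support program following the 12-week intervention phase". The length, reminders, moderated chats and mentor cover of this second run are not described.
- **Technical Development:** "This website would also need to digitally capture and record all interactions between participants".
- **Sample Size:** for 15% dropout and 70% weekly chat participation, "a sample size of 30 would allow us to be 90% confident" that the estimates are accurate within 22 and 28 percentage points respectively.
- **Primary Outcome:** eight criteria, whose count drives a stop, modify or continue decision. None names a trial arm.

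**The concern.** The primary outcome is feasibility, not a contrast between arms. Anyone who uses the program can therefore inform it, including caregivers who start after the waitlist period. The plan gives those caregivers the program and builds the logging, but explicitly leaves them out of the ratings named in the primary objective. For logged usage it does not say whether they count.

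The sample-size rationale raises the same question from the other side. It justifies 30 caregivers partly by the precision of chat participation, although half of them cannot join a chat during the 12-week phase. At stake are the amount of rating data behind the primary objective, the precision of some usage criteria, and a stated precision that does not match the design unless an unstated rule applies.

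**Working it through.** **Inputs.** N = 30 caregivers (Recruitment); 1:1 allocation, so 15 per arm (Allocation); 7 planned mentors (abstract, Methods), of whom 5 had been trained at the time of writing (Results); 15% dropout, 70% chat participation and 90% confidence (Sample Size).

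**Step 1. Reproduce the stated precision.** The Wald 90% full width is 2 × 1.645 × √(p(1−p)/n).

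- Dropout, p = 0.15, n = 30: 2 × 1.645 × √(0.1275/30) = 21.4 points (stated: 22).
- Chat, p = 0.70, n = 30: 2 × 1.645 × √(0.21/30) = 27.5 points (stated: 28).

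Both figures match as full widths rounded up. As margins they would be ±10.7 and ±13.8. The chat figure therefore assumes 30 people.

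**Step 2. Chat precision with those who have access in the 12-week phase (p = 0.70).**

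| People counted | n | Full 90% width | Half-width |
|---|---|---|---|
| Intervention-arm caregivers | 15 | 38.9 | ±19.5 |
| All 30 caregivers | 30 | 27.5 | ±13.8 |
| Intervention-arm caregivers + 7 mentors | 22 | 32.1 | ±16.1 |
| All caregivers + 7 mentors | 37 | 24.8 | ±12.4 |

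The ratio of 15 to 30 caregivers is 38.9/27.5 = 1.41. The chat criterion itself counts mentors and caregivers together, so 22 versus 37 is its own comparison. With 5 mentors it would be 20 versus 35. The dropout figure is unaffected, because the abstract has both groups complete postintervention questionnaires.

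**Step 3. Which of the eight criteria change if only the intervention arm counts.**

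| Criterion | Denominator | Effect |
|---|---|---|
| Mentor weekly participation | mentors | none |
| Weekly mentor contacts | mentors | none |
| Mentors ever contacted | mentors | none |
| Attrition | caregivers, both arms | none |
| Caregiver weekly participation | caregivers | 30 to 15 |
| Caregivers contacting a mentor | caregivers | 30 to 15 |
| Forum use | mentors + caregivers | 37 to 22 |
| Live chat use | mentors + caregivers | 37 to 22 |

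The caregiver participation criterion prints its threshold as a share of mentors. It is read here as a share of caregivers, as its opening words indicate. The fall from 37 to 22 is 15/37 = 41%.

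**Step 4. Effect on one halved criterion.** This is the binomial chance of meeting ≥60% caregiver participation (at least 9 of 15, or 18 of 30).

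| True rate | n = 15 | n = 30 |
|---|---|---|
| 50% | 0.304 | 0.181 |
| 70% | 0.869 | 0.916 |

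The gain is moderate when true participation is poor and small when it is good.

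**The case against.** Four arguments on the other side have weight.

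1. **Usage logs.** The intervention-arm restriction is written only for the evaluation questionnaire. A reader might infer that waitlist usage logs are discarded, but no section says so, and a condensed article may leave their handling to the full protocol. This stands. For logged use, the point is only that the article is silent while its own precision figure needs an answer.
2. **How many criteria are affected.** A reader might infer that the data behind the feasibility criteria are halved. Step 3 shows this for two of eight. Two more shrink by about 41%, and four do not change.
3. **The decision.** A reader might also infer that the continue decision rests on chance. The documents do not support that. The decision counts criteria met, one extra pass matters only at a category boundary, and Step 4 concerns a single criterion. Nor do the minimum numbers in Recruitment bear on this point: they are enrolment minimums for the whole sample, not for one arm.
4. **Comparability.** The second run is undescribed, and forum and chat use is interactive, so participants within a cohort are likely correlated. Two runs of 15 are not 30 independent observations. This stands, and it argues against making a pooled result the main basis for the decision.

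None of this touches the explicit restriction of the ratings or the n=30 basis of the chat precision.

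**Conclusion.** The point holds in a limited form. Ratings that belong to the primary objective will come from about 15 of the 30 caregivers who eventually use the program, by explicit restriction. The stated chat precision (27.5 points full width, given as 28) is not reached in the randomized phase, where it is 38.9 points for caregivers alone or 32.1 with 7 mentors. With 30 caregivers as its base, it is met only if waitlist use after crossover counts, which the article neither states nor excludes.

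The results assume exactly 15 caregivers per arm, all 7 mentors active, no waitlist dropout and independent participants. Dropout and within-cohort correlation both reduce the gain from adding the waitlist cohort, so the n=30 and n=37 figures are upper bounds on precision. The randomized comparison of health outcomes is not in question.

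**What to change.** 1. **Upon Program Completion:** give the same program evaluation to waitlist caregivers after their first 12 weeks of access.
2. **Primary Outcome:** state that the stop/go count is based on the randomized-phase cohort. Report caregiver participation, forum use, chat use and mentor contact for the waitlist cohort over its first 12 weeks of access, separately. Pool the cohorts only as a supplement, and only if the second run is delivered in the same way.
3. **Sample Size:** restate the chat precision for the denominator actually used, for example ±16.1 points for 15 caregivers plus 7 mentors, and say whether the figure is a margin or a full width.
4. Leave the week-12 randomized comparison unchanged.

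**Cost.** One more questionnaire round and analysis of logs that the site already keeps. The final summary comes about 12 weeks later, but the stop/go count need not wait. If a second run with the same moderation and mentor cover is not already planned, delivering it would take staff and mentor time. The second cohort also joins a forum with existing content, which is a further reason to report by cohort.

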### Data Collection

#### At Baseline

A blinded assessor will collect the demographic and health information from participants in both the intervention group and control group and administer the exploratory caregiver- reported measures (listed in Table 1) through email or over the phone (as per the participants’ preference). Our research team has previously used this battery of questionnaires identifying that completion takes approximately 30-40 minutes.

#### Upon Program Completion

We will ask participants (intervention arm only) to complete a program evaluation (through telephone or email, depending on preference). The program evaluation will assess the acceptability through a series of questions (eg, about the helpfulness of the program, how likable program was; 5-point Likert scale; generally, 1=very unacceptable; 5=very acceptable). The evaluation will assess satisfaction by asking participants the extent to which they agree with a series of questions about the program content, delivery, and outcomes (5-point Likert scale; 1=disagree; 5=agree) [45]. Finally, the evaluation will assess the usability by asking participants the extent to which they agree with a series of questions about the usability of various program features (5-point Likert scale; 1=strongly disagree; 5=strongly agree) [46]. We will invite participants to complete a semistructured qualitative interview to further explore their experience with the peer support program (eg, which features were most beneficial, what aspects were most challenging, what can be improved, what should be kept the same) and their perspectives on the support received from peers (eg, quality of support, influence on their caregiving experience). We will host 1-2 focus groups with the peer mentors using GoToMeeting. Using a semistructured interview guide, we will explore their experiences and perspectives of the Web-based program as trained peer mentors. Furthermore, we will audiorecord interviews and focus groups and transcribe verbatim.

## Results

We recruited 5 caregivers to be trained as mentors. The mentor training was completed in July 2018. We have recruited 4 caregivers to participate in the Web-based peer support program. We anticipate initiating the support program September 2018. Results are expected by early 2019.

Two caregivers have beta-tested the peer support website and issues identified have been addressed. Below are screenshots of the initial log-in page (Figure 1), home page (Figure 2), profile set-up page (Figure 3), and private chat function (Figure 4).

**Figure 1 figure1:**
[figure not shown]
Screenshot of the initial log-in page.

**Figure 2 figure2:**
[figure not shown]
Screenshot of the home page.

**Figure 3 figure3:**
[figure not shown]
Screenshot of the profile set-up page.

**Figure 4 figure4:**
[figure not shown]
Screenshot of the private chat function.

## Discussion

This study will result in the production and initial evaluation of a rigorously developed, evidence- and stakeholder-informed peer training and peer support program for caregivers of VAIs residing at home. Burdened and stressed caregivers may experience significant negative physical and emotional consequences to their own health, which may then impact their ability to care for VAIs who themselves are exceptionally vulnerable. Despite a growing body of evidence supporting the effectiveness of peer support interventions [20], there are currently no support programs of this nature tailored to caregivers of VAIs. The evaluation of the peer support program will highlight whether the inclusion of multiple communication tools is feasible, usable, and effective. The evidence generated will inform future iterations of the program so that it includes only the most valuable tools and optimizes them to enable support exchange.

The Web-based peer support program aims to empower community-residing VAIs and their caregivers to manage diseases necessitating mechanical ventilation. We anticipate that if caregivers have better health and quality of life, they will be better able to care for their loved ones who use ventilators. This can help VAIs remain in their homes and, thereby, mitigate the declines in health and quality of life associated with residential care placement [7].

Perceived strengths of this study include the intervention’s social networking-style interface that is likely to be familiar to participants, thereby enhancing the potential for greater usage and better usability of the peer support program. In addition, we anticipate that having multiple features on the website (eg, private chat, discussion forum, and live weekly chat) will increase the likelihood that participants will engage with and benefit from this peer support hub. Finally, the mixed-method nature of this research will not only provide insight into usage patterns and changes in health outcome scores but will also allow for an in-depth exploration of participants’ experiences with the websites and perceptions of how it has influenced their health and caregiving experience. As this is a feasibility study, it is not our objective to test significance. However, we are aware that this limits our ability to comment on the findings’ relevance and have identified it as a goal for future evaluations of the peer support program. While the inclusion of multiple Web-based features has the potential to increase engagement, there is still a possibility that the study will be limited by attrition.

## Abbreviations

HMV: home mechanical ventilation
RCT: randomized controlled trial
VAI: ventilator-assisted individual

## Appendix

Multimedia Appendix 1 Peer review report (for grant funding from Muscular Dystrophy Canada).
